### Risk management

Internet interventions used in the present study were not designed to provide crisis support for persons experiencing suicidal crises. We will exclude individuals with suicidal ideations and refer them to adequate services. We will also monitor participant mood using daily diary measures during the first and last week of the intervention and weekly throughout the intervention, by contacting participants through a chat function to assess any risk. In instances of crisis, we will organise a meeting with our team of psychotherapists and provide crisis support or refer the individual to an adequate service (psychotherapy, psychiatrist, or hospital).

### Interventions

The interventions are self-help digital programs that will be provided to participants through an online delivery platform. The participants will gain access to their randomly selected intervention via a self-generated password and email address. Access to programs will be provided for 8 weeks; the programs will be 6-week long. All conditions will include an anonymous chat function whereby participants can share opinions and ask the research team for help. The participants will also receive minimal therapeutic support. To this end, they will receive weekly emails introducing new program modules and containing motivating prompts. Additionally, once a week, they will receive a message on chat. The aim of this communication is to assess the mood of participants and provide brief feedback on their work to enhance their motivation.

#### Internet CBT-UP intervention

The cognitive-behavioural intervention developed for this study is based on transdiagnostic CBT principles of the UP [50]. Three systematic reviews, with two meta-analyses, have been conducted to evaluate the efficacy of the UP. These reviews reveal that the UP significantly improves anxious and depressive symptoms with moderate to large effect sizes [51, 52]. Our iCBT-UP is a modular intervention consisting of six components teaching different skills for responding to strong negative emotions and emotion regulation difficulties and associated anxiety, depression, and related disorders. Several modifications were made to the original UP in developing the iCBT-UP. These include shortening the intervention program from 8 to 6 modules (see Table 1 for information). This procedure was implemented because of high dropout rates in longer online interventions. The introduction (module 1) and summing-up part (module 8) in the iCBT-UP intervention are not considered treatment modules; they have been shortened to focus exclusively on main goals and are presented as a “pop-up” section upon first entering the intervention site and after completing all modules.

**Table 1 Tab1:** Overview of iCBT-UP intervention

Number	Name	Description
Introduction		Participants learn about objectives of the program and can set their own goals
Module 1	Understanding Your Emotions	Participants learn about the nature and function of emotions. Users learn that all emotions can be broken down into 3 components: thoughts, physical sensations and behaviours, and that each interacts with the others
Module 2	Mindful Emotion Awareness	This module introduces mindful emotion awareness as a skill to use in response to emotion. The two components of this module are present-focused awareness and non-judgemental awareness. Participants can practice these components by audio guided exercises
Module 3	Flexible Thinking	Participants learn about the relationship between their emotions and thoughts. They have a chance to acknowledge their thoughts in different situations, learn about thinking traps and practice flexible thinking
Module 4	Emotional Behaviours	Participants learn about the relationship between their behaviours and emotions. They come to know what we understand by emotional behaviours and think about how they express themselves in their own lives. In the exercises, they learn how to change emotional behaviours
Module 5	Facing Physical Sensations	Participants learn about the effect of physical sensations. They induce physical sensations and learn how to tolerate and accept them
Module 6	Emotion Exposures	At the end, participants set a hierarchy of emotionally difficult situations and conduct emotion exposures
Summary		A brief summary of the content of all modules; relapse prevention

The iCBT-UP used in this study is an interactive intervention with text and audio materials, videos, quizzes, pictures, and gap-filling exercises. Each module consists of an introductory part—with a short video and text and an examination of previous knowledge—followed by a didactic component with activities to train new skills and personal stories where the participants become acquainted with the experiences of two students who are followed throughout the program.

We will recommend completing one module per week, but participants will have the option to complete the program at their own pace.

#### Internet progressive muscle relaxation training (iPMR)

Training in the comparison condition is based on PMR principles [53]. Studies have shown that relaxation reduces stress, anxiety, and depression among university students [54]. One of the most often used researched relaxation techniques is PMR [55]. PMR has been proven to reduce college students’ anxiety and stress and boost happiness [56, 57]. In the present study, we want to evaluate whether changes obtained in iCBT-UP will be significantly higher, than those obtained in an active, well-researched comparator. The PMR training aims to teach how to quickly achieve a state of relaxation. It is also a modular intervention. It consists of five modules (the first module lasts 2 weeks). See Table 2. Participants are asked to practise techniques from each module twice a day. The intervention is also interactive and contains videos introducing new topics to participants and audio-guided relaxations.

**Table 2 Tab2:** Overview of iPMR intervention

Number	Name	Description
Module 1	Progressive Muscle Relaxation of 16 Group of Muscles	Participants learn how to tighten and relax 16 groups of muscles. This module is recommended to last for 2 weeks
Module 2	7 Muscle Group Relaxation	This is a shortened version of PMR. Participants learn how to tighten and relax 7 groups of muscles (first arm, second arm, head, neck, torso, first leg, second leg)
Module 3	4 Muscle Group Relaxation	This is a shortened version of PMR. Participants learn how to tighten and relax 4 groups of muscles (arms, head, torso, legs)
Module 4	Release Only Condition	Module in which participants are taught to obtain a state of relaxation without tightening muscles
Module 5	Your Own Experience	In this module, participants are engaged to train relaxation on their own—without audio recordings. They can do so in different situations in their daily lives and in different body positions

#### Waiting List Control (WLC)

We included the WLC condition to evaluate, if changes obtained in the iCBT-UP group can be attributed to the intervention, rather than simply the passage of time. This group will receive access to active intervention (iPMR or iMBCT) after the 6-week waiting period and completion of the post-treatment assessment.

### Measures

A summary of all measures and time points is presented in Table 3.

**Table 3 Tab3:** A description (SPIRIT diagram) of enrolment, intervention, and assessment

	**Study period**						
	**Enrolment**	**Allocation**	**Baseline**	**During the 6 weeks interventions**		**Post assessment**	**Follow-up**
**Timepoint**	***-t***_***1***_	**0**	***t***_***1***_	***Daily Diaries week (1–7 day of intervention)***	***Daily Diaries week (36–42 day of intervention)***	***t2*** ***(1 day after the intervention)***	***t3*** ***(30 days after the intervention)***
**Enrolment:**							
**Eligibility screen**	X						
**Informed consent**	X						
**Allocation**		X					
**Interventions:**							
***iCBT-UP***				X	X		
***iPMRT***				X	X		
***Waiting list***				X	X		
**Assessments:**							
***MINI***	X						
***IADQ***	X					X	X
***PHQ-9***	X					X	X
***GAD-7***	X					X	X
***SWLS***			X			X	X
***AAS***			X			X	X
***PSS-10***			X			X	X
***FFMQ-15***			X			X	X
***AAQ-II***			X			X	X
***SCS-SF***			X			X	X
***CFQ***			X			X	X
***PTQ***			X			X	X
***WEMWBS***			X			X	X
***Daily diaries***				X	X		
***Cognitive task***			X			X	X
***Adverse events***						X	

#### Diagnostic measure

The Mini-International Neuropsychiatric Interview (MINI) [58] is a short diagnostic interview based on DSM-5 criteria, which focuses on the existence of current psychiatric disorders. It consists of separate modules to diagnose specific disorders.

#### Questionnaires

##### Primary outcome measures

The International Adjustment Disorder Questionnaire (IADQ) [59] is a 19-item questionnaire used to assess AjD related to ICD-11 criteria [13]. The IADQ consists of nine item stressor list, three items that assess preoccupation with the stressor, three items that consider symptoms of failure to adapt, three items that assess functional impairment, and one item that assess duration of symptoms. The primary endpoint for this outcome is immediately post intervention. Then, we will assess it after a one-month follow-up to evaluate the stability of the obtained changes. We will compare post-test scores between three conditions as well as change from baseline measurement.

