## Methods/design

### Study design

This study is a parallel group randomized controlled trial (RCT). The participants will be allocated to one of three 6-week conditions: (1) online cognitive behavioural therapy, based on the unified protocol (iCBT-UP); (2) online progressive muscle relaxation training (iPMR, active control group); and (3) waiting-list control group (WLC). The last group will receive access to their chosen intervention after the waiting period (6 weeks). To help WLC participants maintain motivation, weekly emails will be sent to remind them of the study and to assess their mood. They will be instructed to contact the research team in instances of any crisis. At that point, they will be administrated by our team psychotherapist or psychiatrist and referred to an adequate service. Assessments will consist of questionnaires, a cognitive task and a study of daily diaries. All assessments will be administered through an online data collection platform delivered by organisers (Supporty.pl), occurring at (1) screening, (2) baseline (prior to randomization), (3) at the end of the 6-week online program (or waitlist period), and (4) 1 month after finishing treatment (for participants in the active intervention conditions). Daily diary studies will be carried out for entries in the first and again in the last week of the interventions. Cognitive task will be administered at baseline, at the end of 6 weeks of online intervention, and 1 month after finishing treatment. The study will follow SPIRIT guidelines (Standard Protocol Items: Recommendations for Interventional Trials) [47].

Figure 1 shows the trial design. The study protocol and informed consent have been approved by the Ethics in Research Committee of the Faculty of Psychology, University of Warsaw.

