### Participant recruitment and inclusion and exclusion criteria

Participants will be recruited using announcements in popular social media and university newsletters. The study will be advertised to Polish students from different universities around the country. Interested participants will provide informed consent and then complete screening questionnaires. Those meeting preliminary eligibility criteria will then be assessed using the Mini-International Neuropsychiatric Interview (MINI) to ensure they meet Diagnostic and Statistical Manual of Mental Disorders, Fifth Edition (DSM-5) [48] diagnostic criteria for an AjD as a primary diagnosis and to establish comorbidities. The diagnostic interview will be administered by a trained psychologist or psychotherapist by video conference and then entered to the database.

The inclusion criteria consist of having student status, being 18 years old or older, having access to the internet and using a computer or smartphone, and meeting the diagnostic criteria of AjD in the IADQ questionnaire and meeting diagnostic criteria for AjD in the MINI.

The exclusion criteria consist primarily of conditions that require prioritization for immediate or simultaneous treatment: specifically, an increased risk of suicidality intent or ideation, bipolar and psychotic disorder, and/ or alcohol/substance use disorder. Individuals will also be excluded if they are receiving another psychological treatment at the start of the study or have no time to participate in the program. Pharmacological treatment during the intervention period will be allowed, provided that the type and dose of medication are stable for 6 weeks before study involvement.

Individuals not meeting the inclusion criteria will be referred to adequate services.

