### Randomization and blinding

Subjects who meet the inclusion criteria will be randomized to one of two active groups or the waiting-list group using a 2:2:1 allocation ratio. The participants will be randomly allocated using a computerized block randomization, using block sizes of 6. Random allocation will be performed using an algorithm developed by a computer scientist and executed independently of the research team by an independent program [49]. The main researcher will then reveal the concealed allocation and inform participants of their placement into one of three groups. Randomization will be stratified based on the score of the initial AjD questionnaire assessment (the IADQ; see description below). The principal investigator responsible for determining study eligibility will be blinded to the randomization sequence. The researchers and psychotherapists leading the study and contacting participants cannot be blinded to allocation for practical reasons; however, those conducting the MINI evaluation will be blind to the condition allocation during the assessment.

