### Sample size calculation

The sample size was determined in relation to the between-group effect size and calculated using G*Power software. Previous research on an online UP intervention and online interventions for AjD has revealed a between-group effect size at the level of *d* = 0.5 and a within-group effect size at the level of *d* = 0.63 [42, 87]. Assuming an alpha 0.05 with a power of 0.80 and post-treatment between-group effect size of *d* = 0.5 (iCBT-UP versus control), 190 participants in the three groups will be sufficient to detect assumed differences. However, because the literature reveals dropout rates from online CBT interventions, with minimal guidance, of approximately 30% [88], a total sample of 247 participants will be recruited.

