### Governance and oversight of the trial

We will establish a trial management group (TMG) that will oversee the whole process of the research—recruitment of participants, assessments, ethical issues, adverse events, and data management. This group will meet once a week during the active phase of the research and in every case as the need arises. The group will consist of the principal investigator, the supervisor and co-principal investigator, and the trial platform manager. Due to the latest recommendations, adverse events will be investigated twofold. First is using our questionnaire outcome measures—to determine the number of patients who deteriorated and those who did not respond to the treatment. Second is using a self-report measure to detect adverse events administered post-treatment (described above) [85]. In case of any changes to the protocol, the TMG will communicate them to the investigators and participants and record them in the study diary.

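### As scheduled, the only pre-treatment IADQ score is the one that admits the participant, so within-arm improvement is overstated and deterioration undercounted; the between-arm comparisons are not biased

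*Protocol article*

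**What the plan says.** The Study design section of the protocol article lists screening and baseline as two separate assessments: "occurring at (1) screening, (2) baseline (prior to randomization". Entry requires "meeting the diagnostic criteria of AjD in the IADQ questionnaire and meeting diagnostic criteria for AjD in the MINI". The screening questionnaires come before the diagnostic interview: "Those meeting preliminary eligibility criteria will then be assessed using the Mini-International Neuropsychiatric Interview (MINI". The same score is used in allocation: "Randomization will be stratified based on the score of the initial AjD questionnaire assessment".

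In Table 3, the IADQ, PHQ-9 and GAD-7 are marked at enrolment (-t1), post-assessment (t2) and follow-up (t3), and not at baseline (t1). The other nine questionnaires and the cognitive task are marked at t1, t2 and t3.

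Two stated uses need a pre-treatment value. Under Primary outcome measures, the IADQ analysis is described thus: "We will compare post-test scores between three conditions as well as change from baseline measurement". Under Governance and oversight, the first of two ways of investigating adverse events uses the questionnaire outcomes "to determine the number of patients who deteriorated and those who did not respond to the treatment".

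**The concern.** Taken together, these statements mean that the baseline for the primary outcome is the screening score that let the participant in. Part of any high score is temporary fluctuation or measurement error, and selecting on the score selects for that part. On re-measurement it fades, so the group mean falls even if nothing was done.

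Three quantities lean in a known direction: within-arm improvement looks larger, more participants appear to respond, and fewer appear to deteriorate. The last matters most, because that count is meant to detect harm and the artefact hides harm. At t3 only the active arms are followed, so change from screening to follow-up has no waiting-list group from which the fall could be read off.

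For the PHQ-9 and GAD-7 the point is narrower. No entry cut-off on either is stated. The issue for them is mainly that their pre-treatment time point differs from that of the other measures.

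**Working it through.** **No figure of the plan to reproduce.** The protocol does not quantify this. The sample size rests on a post-treatment between-group effect of d = 0.5 and is not changed by the point. The nearest benchmark is the within-group effect of d = 0.63 cited in the Sample size calculation section.

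**Inputs**
- From the documents: entry depends on the IADQ; there is no IADQ at t1; change, deterioration and non-response are to be derived.
- Assumed, because the documents do not give them: the share q of screened students who pass the IADQ (20-70%), the test-retest correlation r (0.6-0.9), normally distributed scores, and entry as a single cut-off on the total score.

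**Expected fall with no treatment effect and no time trend**, in SD of the screened population:

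fall = (1 - r) × φ(c)/q, where c is the cut-off that a share q exceeds and φ is the normal density.

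Worked case, q = 50%: φ(0)/0.5 = 0.399/0.5 = 0.80. With r = 0.8 the fall is 0.2 × 0.80 = 0.16; with r = 0.6 it is 0.4 × 0.80 = 0.32.

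| Share passing | r = 0.6 | r = 0.7 | r = 0.8 | r = 0.9 |
|---|---|---|---|---|
| 20% | 0.56 | 0.42 | 0.28 | 0.14 |
| 35% | 0.42 | 0.32 | 0.21 | 0.11 |
| 50% | 0.32 | 0.24 | 0.16 | 0.08 |
| 70% | 0.20 | 0.15 | 0.10 | 0.05 |

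Against 0.63, the extremes are 0.05/0.63 = 8% and 0.56/0.63 = 89%. This is a rough scale only, because the SD behind 0.63 may not be the screened-population SD.

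**Simulation under no effect** (q = 20% or 50%, r = 0.7 or 0.8). Reliable change is taken, as an assumption, to be a difference beyond 1.96 × √(2(1 - r)).

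| Result among those admitted | From the screening score | From a separate baseline |
|---|---|---|
| Mean change | -0.16 to -0.42 SD | 0.00 SD |
| Reliable improvement | 3.9-6.6% | 2.5% |
| Reliable deterioration | 0.4-1.1% | 2.5% |

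The between-arm difference in change from screening stayed within 0.01 SD of zero. At re-measurement, 20-44% of those admitted had fallen below the entry cut-off with no effect at all. The simulated PHQ-9 change was 0.00 SD when its errors were independent of the IADQ errors.

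**The case against.** **The main comparison is safe.** The primary endpoint is the IADQ immediately after the intervention, compared between randomised arms, and the waiting list is there to separate treatment from change over time. This stands. A reader might infer that the planned analysis of change is biased as a whole. It is not: between-arm change is as well protected as the post-test comparison. Maintenance can also be judged from t2 to t3, which does not use the screening score.

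**The size is assumed.** This also stands. Self-referred volunteers may pass at a high rate, which moves the fall towards the low end. The MINI is a second, separate gate that tends to keep people whose elevation is real, and the model ignores it. The IADQ criteria cover several components, so one cut-off on a total is only a proxy. The direction does not depend on these choices, but the size does.

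**Three further inferences go beyond the documents.**
- That all three scales were selected for being high. Only the IADQ is stated as an entry criterion.
- That an outdated baseline costs precision. The interval from screening to baseline is not given, so the loss cannot be assessed.
- That mediation is distorted because mediators start at t1 and the outcome at -t1. The Data analysis section does not say that mediation uses change scores, and the gap may be short.

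**It may be a slip in the table.** The abstract says that assessments take place at baseline, and the outcome section speaks of a baseline measurement of the IADQ. If a t1 IADQ is intended, Table 3 needs correcting. If not, the outcome section should say that baseline means the screening score. The text has to change either way.

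**Conclusion.** The point holds for within-arm change and for absolute counts. With the schedule as printed, regression to the mean overstates improvement and response on the IADQ in every arm and understates deterioration. The untreated fall is about 0.05-0.56 SD of the screened population for pass rates of 20-70% and test-retest correlations of 0.6-0.9. In the narrower simulated range, apparent reliable deterioration drops from 2.5% to 0.4-1.1%. These figures illustrate and do not estimate: neither input is in the documents, and the MINI gate may lower them.

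The randomised comparisons at t2 are not biased, and the sample size is unaffected. This is an inexpensive improvement to a schedule, and it is needed at the protocol stage because no later analysis plan can supply a measurement that was not taken.

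**What to change.** 1. In Table 3, mark the IADQ at baseline, completed after the MINI and before randomisation. Mark the PHQ-9 and GAD-7 there too, so that all questionnaires share one pre-treatment time point.
2. Reconcile the order. Table 3 prints allocation (0) before baseline (t1), whereas the Study design section puts baseline before randomisation. Unless this is settled, a new mark at t1 could be read as a post-allocation baseline.
3. Keep the screening IADQ for eligibility and stratification. State that the baseline score is the reference for change, covariate adjustment, response and deterioration, and let it play no part in eligibility.
4. If response is to mean no longer meeting the IADQ criteria, report how many already fail to meet them at baseline. A new reference score does not by itself remove the fall from that kind of count.

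The cost is up to 19 (IADQ) + 10 (PHQ-9 with its additional statement) + 7 (GAD-7) = 36 short online items at an assessment that already takes place, with some added participant burden. Within-arm change will look less favourable. The removal to 0.00 SD in the simulation assumes that fluctuations at screening and baseline are independent; if the two are very close in time, less of the fall is removed.

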### Data analysis

All data will be analysed using the Statistical Package for the Social Sciences (SPSS) version v21.0 (IBM Corporation, Armonk, NY, USA). All randomized participants will be analysed, including those who stop receiving treatment on an intention-to-treat (ITT). The multiple imputation method will be used for missing data when appropriate. We also plan to perform sensitivity analysis to test the robustness against departures from the assumption of missing data being at random following the technique explained in Crameri et al. [89]. Hierarchical linear modelling will be used to assess our primary and secondary outcomes, daily diary results, and cognitive functioning. The most detailed level of analysis will contain results from daily diary measurements. The next level will be based on differences between each measurement. The last level in the model will include differences between each of the three groups. Hayes’ Process Macro will be used to assess mediation effects [90]. In this approach, effects are assessed using bias-corrected bootstrap confidence intervals. These effects are considered significant if the upper and lower bounds of the bias-corrected 95% confidence intervals do not contain zero. Mediation is assessed through the indirect effect of the independent variable on the dependent variable, mediated by an intermediate variable. For each statistically significant result, effect size will be calculated. The number of times each participant uses the program will be used to measure adherence. The results of this study will be submitted for publication in a peer-reviewed journal.

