## Discussion

To our knowledge, there is no published study evaluating the effectiveness of an online psychological intervention for students experiencing AjD. Our study is meant to fill this gap. The study aims to examine the effectiveness of an internet psychological intervention for students experiencing AjD. Further objectives are to explore mechanisms for obtained changes. We expect that the online UP intervention will be an effective form of treatment, and we expect that obtained changes will be significantly greater than those from the two control conditions. We also predict that experiential avoidance, mindfulness skills, self-compassion, and cognitive fusion will mediate this effect.

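### Two comparisons of the primary outcome are named without saying which decides, and no stated analysis adjusts for the baseline IADQ score on which randomisation is stratified

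*Protocol article*

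**What the plan says.** Under Primary outcome measures, the protocol article names one instrument, the IADQ, and one time point: "The primary endpoint for this outcome is immediately post intervention". It then fixes two comparisons at that point: "We will compare post-test scores between three conditions as well as change from baseline measurement".

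Three other places bear on which comparison is meant:

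- Sample size calculation sizes the trial on a post-treatment difference: "Assuming an alpha 0.05 with a power of 0.80 and post-treatment between-group effect size of" d = 0.5.
- The Discussion words the hypothesis as change: "we expect that obtained changes will be significantly greater than those from the two control conditions".
- Data analysis gives a third description: "Hierarchical linear modelling will be used to assess our primary and secondary outcomes, daily diary results, and cognitive functioning". Of its levels it says "The next level will be based on differences between each measurement", with a further level for the three groups. Covariates are not stated.

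On the design side, Randomization and blinding says "Randomization will be stratified based on the score of the initial AjD questionnaire assessment", and allocation is made "using a 2:2:1 allocation ratio", with the waiting list as the smallest arm.

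**The concern.** The post-test score and the change score are different estimators of the same treatment effect. In one dataset they can give different estimates and different p-values. The sample size rests on one, the hypothesis is worded as the other, and the outcome definition keeps both. A reader of the results could not tell which was meant to decide.

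Neither raw comparison is the efficient one. The raw post-test score ignores a baseline that predicts the outcome, and the raw change score over-corrects for it. The trial also uses that baseline to balance the arms. If the analysis leaves it out, the test does not credit the balance that stratification bought, and its standard error is too large. What is at stake is clarity about the primary result, and power for the contrast with the smallest arm.

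**Working it through.** **The plan's own figure.** With two-sided alpha 0.05, power 0.80, d = 0.5 and equal arms, n per arm = 2 × (1.960 + 0.842)² / 0.5² = 62.8, so 63. Three arms give 189, against the stated 190. This is the sample size for a raw post-test comparison with equal arms.

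**Numbers for iCBT-UP versus waiting list.** The article recruits 247, expects about 30% dropout and allocates 2:2:1. Then 247 × 0.7 = 172.9; one fifth is 34.6 (35) and two fifths is 69.2 (69).

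**Variance factors.** Assume equal SDs at baseline and post-test, and let r be their correlation. Relative to the variance of the post-test score:

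- post-test score: 1
- change from baseline: 2(1 − r)
- baseline-adjusted post-test score: 1 − r²

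The adjusted factor is never the largest. It is (1 + r)/2 times the change factor, and below 1 for any r other than 0. The article gives no r, so 0.4 to 0.7 is assumed.

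**Power.** The noncentrality is (0.5/√factor) × √(69 × 35/104). Here √(69 × 35/104) = 4.819, so the post-test score has noncentrality 0.5 × 4.819 = 2.41. With a two-sided t-test at 0.05:

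| r | Post-test | Change | Adjusted |
|---|---|---|---|
| 0.4 | 0.67 | 0.59 | 0.74 |
| 0.5 | 0.67 | 0.67 | 0.79 |
| 0.6 | 0.67 | 0.76 | 0.85 |
| 0.7 | 0.67 | 0.87 | 0.92 |

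With all 190 evaluable (76 versus 38) and r = 0.5, the row is 0.70, 0.70 and 0.82.

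**Effect of stratification on the unadjusted tests.** I simulated the null at 2:1 (70 versus 35), with exact balance inside two or four baseline strata; the number of strata is illustrative. A nominal 5% test of the post-test score rejects 3.1% (two strata) or 2.7% (four) of the time at r = 0.5, and 1.9% or 1.0% at r = 0.7. The change-score test rejects 2.4% to 3.8% of the time over r = 0.4 to 0.7. The adjusted test stays at about 5% throughout. The unadjusted standard errors are therefore too large. At d = 0.5 the same simulation puts the power of the raw tests at most about 0.05 above the table, and the adjusted test remains the most powerful at every r.

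**The case against.** **The article does not say that the analysis is unadjusted.** This stands. The Data analysis section names a hierarchical model without its covariates, and an analysis plan that is not shown may settle them. The fair statement is that no stated analysis conditions on baseline. Naming the model does not close the gap, however. If baseline is one of the repeated outcomes and each arm has its own baseline mean, the group-by-time term with complete data is the raw change comparison.

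**Adjustment would be a gain over the plan, not a loss from it.** This is partly right. The sample size assumes a raw post-test difference, and the 0.67 comes from 2:2:1 allocation and attrition, which are separate matters. At r = 0.7 the advantage over change is small (0.92 against 0.87). But the gain costs nothing, and at r = 0.5 it brings either raw comparison from 0.67 to 0.79.

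**A reader might infer that two tests of one endpoint double the false-positive rate.** The documents do not support that. If stratification is ignored, the chance that at least one of the two tests is significant is about 9% per contrast, and about 16–17% over two tests on two contrasts. But randomisation is stratified on the baseline score, which makes unadjusted tests conservative. With two to four strata the simulated rates fall to about 4–6% per contrast and 7–11% over all four tests, roughly what two uncorrected contrasts alone would give. Nor does the article say that one success in four would be claimed; its hypothesis is superiority to both controls.

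**A reader might also object that the IADQ baseline is the eligibility score, so change carries regression to the mean.** That affects change within an arm. It is expected equally in all randomised arms and does not bias the between-group comparison.

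**Conclusion.** The point holds as one of specification and efficiency. The article fixes two comparisons of one primary endpoint, designates neither, and does not connect either to its hierarchical model. No stated analysis uses the baseline IADQ score on which randomisation is stratified. For iCBT-UP versus waiting list at 69 versus 35, adjustment raises power by 0.07 to 0.25 over the post-test score and by 0.05 to 0.15 over change, for r from 0.4 to 0.7. This assumes d = 0.5, equal SDs, a two-sided 5% test and 30% loss from 247. The abstract's smaller target of 214 would lower every figure without changing which analysis is most precise. The point does not extend to a doubled type I error or to bias in the randomised comparison.

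**What to change.** Name one primary analysis: the between-group difference in IADQ at t2, adjusted for the continuous pre-randomisation IADQ score and for the stratification factor. It can be fitted as ANCOVA or as the equivalent term in the hierarchical model, with baseline entered as a covariate or the arms constrained to a common baseline mean. State that the change-score comparison is descriptive or supportive, and align the wording in Primary outcome measures, Data analysis and the Discussion with this choice.

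The cost is analysis wording and a few degrees of freedom for the stratification factor. The enrolment IADQ is already collected, so no further data are needed.
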